### Measurement

Between February 18 and March 17, 2023, a pilot survey was conducted on 30 nurses in OR of the Affiliated Hospital of Guizhou Medical University by research assistants, and questionnaires were filled out on site. Based on the pilot test results, the content of the questionnaire was adjusted to form a final version. Subsequently, we started a formal investigation on March 18th, 2023. Officials from Guizhou Medical University, along with the director of the Nursing Department of the Affiliated Hospital of Guizhou Medical University contacted the head nurse in OR of the target hospitals, and research assistants explained the purpose and relevance of the study to them. The head nurse of the OR of the target hospital recruited nurses who meet the inclusion criteria. After obtaining respondents’ verbal consent for data collection, they were issued an electronic questionnaire and an electronic informed consent form. In addition, nurses who completed the questionnaire were be paid 2 RMB for their time and effort. Data collection was scheduled to the end of July 2023, but the exact time depended on the progress of the research.

In this study, the research assistants were trained and qualified nursing master’s students. The training content included the types, structures, question formulations, response types and survey methods of questionnaires by professional courses.

### Bias control

We tried to control for non-response bias by explaining the purpose and value of the study to respondents through phone or email, as people are more likely to respond to the questionnaire when they understand the reason for the survey. Due to the fact that participants’ past experience of noise annoyance and burnout at any time could lead to recall bias, we asked respondents to relate to events that occurred within the past month when filling out the questionnaire. To reduce selection bias to some extent, we chose hospitals in a certain region of China (Guizhou Province) as the research site, and all hospitals are tertiary hospitals. Since all the participants come from tertiary hospitals in the same region, they have basically the same social culture and similar workloads. This makes the results comparable.

### Statistical analysis

We will review the returned questionnaires one by one to check whether they are filled in completely. If the data has obvious regularity or consistency (for example, if you select the same option in the entire questionnaire), the questionnaire will be considered invalid [38], and we will delete it. Excel 2016 will be used to manage data, and IBM SPSS Statistics 26.0 (IBM Corp., 2019) will be used for statistical analysis. For describing the data, the quantitative data conforming to the normal distribution will be represented by the mean and standard deviation after calculating the skewness and kurtosis of the data. Quantitative data that does not conform to the normal distribution will be expressed as medians and interquartile ranges. The comparison of noise annoyance, emotional labor and burnout scores of OR nurses with different general demographic data will be performed according to the results of the homogeneity of variance test. If the variance is homogeneous, we will use independent sample student’s t-test and one-way ANOVA; if not, we will use non-parametric tests (Wilcoxon rank sum test and Kruskal-Wallis H test). In addition, qualitative data will be presented as frequencies and percentages. Pearson correlation coefficient or Spearman correlation coefficient (according to the results of the normality test) will be conducted to explore the correlation between variables. For the correlation coefficient, 0 means there is no correlation between the two, -1 means negative correlation, and 1 means positive correlation. The closer it is to -1 or 1, the stronger the correlation [38].

Potential confounders as contributors to burnout, and possibly related to noise annoyance and emotional labor, were defined a priori and incorporated into the statistical model, such as sex, age, marital status, education level, personality traits, health status, work experience as an operating room nurse, professional title, annual income, satisfaction with salary and hospital tenure. We will carry out linear multiple regression analysis to control for confounders and determine whether noise annoyance and emotional labor are contributors to burnout. Before performing multiple regression analyses, we will examine scatterplots of each predictor variable against the burnout score to check for linear relationships. The normality of residuals will be tested using the Shapiro-Wilk test and visualized with Q-Q plots. And we will evaluate homoscedasticity by plotting residuals versus predicted values. The Durbin-Watson statistic will be used to test for autocorrelation of residuals. In case non-linear relationships are identified, we will consider applying transformations to the predictor variables or incorporating polynomial or interaction terms into the regression model to better capture the nature of the relationships.

To address the risk of multicollinearity arising from multiple confounders, we will calculate Variance Inflation Factors (VIF) and tolerance levels for each predictor variable. A VIF value exceeding 5 or a tolerance value below 0.2 will indicate significant multicollinearity [39]. If multicollinearity is detected, we will consider removing highly correlated variables.

We will use Model 4 (PROCESS macro) in SPSS 26.0 to examine the mediation effect of emotional labor on the relationship between noise annoyance and burnout among OR nurses [40]. A nonparametric, bias-corrected 95% bootstrapped confidence interval (BCI) with 5,000 bootstrap iterations will be used to determine the importance of mediating effects. Indirect effects will be deemed significant if the 95% BCI do not contain zero [41,42]. A p-value of 0.05 or lower will be regarded as statistically significant, based on a two-sided test.

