### Participants

Participants will be recruited from 11 hospitals in accordance with the criteria below. The inclusion criteria are: (1) Registered nurses who have worked in ORs for more than 1 year; (2) They should work in the corresponding post in ORs during the investigation period; (3) They provide informed consents and voluntary participation in this study. Visiting fellowship nurses and practical nurses will be excluded in our study.

The required sample size was calculated using G*Power 3.1.9.7 software [26] for multiple linear regression analysis, with four predictor variables: noise annoyance, surface acting, deep acting, and natural emotional expression, and burnout as the outcome variable. While emotional labor is our primary construct of interest, it is operationalized through three distinct dimensions—surface acting, deep acting, and natural emotional expression—each serving as an individual predictor. This differentiation allows for a more nuanced examination of how each aspect of emotional labor contributes to burnout among OR nurses.

The test family used was F-tests, and the statistical test employed was linear multiple regression (Fixed model, R² deviation from zero). A priori: Compute required sample size - given α, power, and effect size, was used for the type of power analysis. Assuming a medium effect size (f² = 0.15), an alpha level of 0.05, and a desired power of 0.95, the minimum required sample size was determined to be 129 participants. To account for a potential 20% dropout rate, the final minimum sample size was calculated to be 155. This sample size ensures sufficient power to detect significant relationships within our multiple regression model [27].

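### Unequal variance is the wrong trigger for rank tests: in the demographic comparisons the type I error leaves 0.05 when group sizes and spreads both differ

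*Protocol article*

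**What the plan says.** The rule is in the protocol article, Statistical analysis, first paragraph. It covers "The comparison of noise annoyance, emotional labor and burnout scores of OR nurses with different general demographic data", and the choice of test "will be performed according to the results of the homogeneity of variance test". There are two branches:

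- Equal variances: "If the variance is homogeneous, we will use independent sample" t-tests for two groups and one-way ANOVA for more.
- Unequal variances: "if not, we will use non-parametric tests (Wilcoxon rank sum test and Kruskal-Wallis H test").

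No unequal-variance test such as Welch's is named. In the same paragraph, normality decides how scores are summarised and whether Pearson or Spearman is used, but it has no part in choosing the group-comparison test. The threshold, at the end of the section, is: "A p-value of 0.05 or lower will be regarded as statistically significant, based on a two-sided test".

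**The concern.** Wilcoxon and Kruskal-Wallis answer non-normality. Read as tests of a shift in location, they assume that the groups share shape and spread under the null. The protocol uses them only when a pre-test has indicated that spread differs, which is when that assumption fails.

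The rule can also separate description from test. A normal score with unequal variances would be summarised by mean and SD but tested on ranks. A skewed score with equal variances would be summarised by median and interquartile range but tested on means.

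At stake is the list of characteristics reported as related to the three scores. If the smaller group has the larger spread, false differences appear too often. If the larger group does, the test is too conservative and real differences are more easily missed. The sample is a convenience sample and nothing balances its subgroups, so some small categories (for example the poorest health status) are plausible.

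**Working it through.** **1. The plan's own figure.** The Participants section gives no figure for the group comparisons. It sizes the regression: "Assuming a medium effect size (f² = 0.15), an alpha level of 0.05, and a desired power of 0.95", "with four predictor variables: noise annoyance, surface acting, deep acting, and natural emotional expression". With noncentrality λ = f² × N = 0.15 × 129 = 19.35 and degrees of freedom 4 and 129 − 5 = 124, power is 0.9506, so "the minimum required sample size was determined to be 129 participants" reproduces. Then 129 × 1.2 = 154.8, rounded up to the stated 155. I use 155 only as a total to split into groups.

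**2. Inputs.** From the document: the rule, two-sided 0.05 and the total of 155. Assumed, because the document gives none: group splits, SD ratios and normal scores with equal means.

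**3. Closed form for Wilcoxon, 130/25, SD ratio 2.** The test takes the variance of the estimated P(X<Y) to be (1/12)(1/m + 1/n). With normal scores, equal means and SDs s₁, s₂, the true variance is approximately A₁/m + A₂/n, where Aᵢ = arcsin[sᵢ²/(s₁² + s₂²)]/(2π). With equal SDs, A = (π/6)/(2π) = 1/12, and the two agree.

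- For SDs 1 and 2: A = arcsin(0.2)/(2π) = 0.03205 and arcsin(0.8)/(2π) = 0.14758.
- Variance used by the test: (1/12)(1/130 + 1/25) = 0.00397.
- Larger SD in the group of 25: 0.03205/130 + 0.14758/25 = 0.00615. Ratio 1.547, square root 1.244. The effective critical value is 1.96/1.244 = 1.576, so the type I error is about **0.115**.
- Larger SD in the group of 130: 0.14758/130 + 0.03205/25 = 0.00242. Ratio 0.608, square root 0.780. The effective critical value is 1.96/0.780 = 2.513, so the type I error is about **0.012**.
- Both variances scale with 1/N, so a larger sample with the same split does not cure this.

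**4. Simulation of the whole rule** (Levene p < 0.05 leads to the rank test, otherwise Student's t or ANOVA). There were 20,000 runs for two groups and 8,000 for three; the Monte Carlo standard error at 0.05 is √(0.05 × 0.95/20,000) = 0.0015 and √(0.05 × 0.95/8,000) = 0.0024. At 130/25 with SD ratio 2 the rule gives about 0.11, and about 0.01 reversed, in line with step 3. Other splits of 155:

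| Groups | SDs (in group order) | Student t / ANOVA | Protocol rule | Welch |
|---|---|---|---|---|
| 77/78 | 1/2 | 0.048 | 0.057 | 0.048 |
| 77/78 | 3/1 | 0.053 | 0.072 | 0.051 |
| 103/52 | 1/2 | 0.109 | 0.086 | 0.048 |
| 103/52 | 2/1 | 0.018 | 0.034 | 0.052 |
| 125/30 | 1/1.5 | 0.123 | 0.088 | 0.052 |
| 125/30 | 1/2 | 0.187 | 0.112 | 0.053 |
| 125/30 | 2/1 | 0.004 | 0.014 | 0.052 |
| 140/15 | 1/2 | 0.250 | 0.131 | 0.052 |
| 140/15 | 2/1 | 0.001 | 0.006 | 0.049 |
| 52/52/51 | 1/1.5/2 | 0.060 | 0.058 | 0.050 |
| 100/40/15 | 1/1.5/2 | 0.184 | 0.108 | 0.052 |
| 100/40/15 | 2/1.5/1 | 0.011 | 0.017 | 0.051 |

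Across all settings run with unequal SDs (ratios up to 3), the rule ranges from 0.001 to 0.16 and Welch from 0.047 to 0.054.

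**The case against.** **The switch is better than no switch in unbalanced groups.** This stands. At 125/30 with SD ratio 2 the rule gives 0.112 where Student's t alone gives 0.187; in reverse it gives 0.014 against 0.004. Both are nearer 0.05. A reader might infer that the rank tests make matters worse; in unbalanced groups they do not. They reduce the problem without removing it. Only with two near-equal groups is the switch slightly worse than Student's t (0.057 against 0.048 at ratio 2).

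**The error rate is not wrong in every unequal-variance comparison.** This also stands. With near-equal groups it lies between about 0.05 and 0.07. A material departure needs imbalance as well as unequal spread, and the document states neither group sizes nor SDs.

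**The comparisons are secondary.** This stands too. A reader might infer that the study's main conclusions are at risk. The documents do not support that: hypotheses a to d rest on correlations, regression and bootstrap mediation. The regression confounders are fixed in advance, so a distorted univariate p-value does not decide which of them enter.

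**Rank tests change the question from means to distributions.** This matters for interpretation, but the protocol does not plan to rank characteristics against one another and does not define a mean difference as the target. I do not press it as a separate fault.

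None of this makes unequal variance a sound reason to choose a rank test, and no other section corrects the rule.

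**Conclusion.** The rule is wrong as written, with limited reach. It names unequal variance as the only reason to use tests that need equal spread to be valid tests of location. If group sizes and spreads both differ, the type I error is about 0.11 or about 0.01 at an assumed 130/25 split with SD ratio 2, depending on which group has the larger SD. If groups are near equal it is 0.05 to 0.07. These sizes rest on assumed splits, SD ratios and normal scores; the direction of the error follows from the tests themselves. The consequence is confined to the univariate comparisons of scores across demographic groups. It is worth correcting because the protocol judges these comparisons at 0.05 and the correction is cheap.

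**What to change.** Replace the rule with Welch's t-test for two groups and Welch's ANOVA for more, with Games-Howell for pairwise comparisons, and drop the variance pre-test. The minimum change is to put these tests in place of the rank tests in the unequal-variance branch.

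If rank tests are also reported for skewed scores, choose them by the normality criterion that the same paragraph already uses, and interpret them as a difference in distribution, not in means.

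The cost is one sentence; the tests are available in the planned software. Welch loses a little power when variances are in fact equal: about 1 to 2 points at 130/25 and about 4 points at 140/15 (0.834 to 0.793 for a difference of 0.8 SD).

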### Ethical considerations

We obtained approval from the corresponding institutional review board (2022 Ethics Review No. 746). The questionnaire contained the following information about the participants: research purpose, and guarantees of anonymity, voluntary participation, and that their personal data would be used only for the purpose of this research. In addition, participants were informed that they had the right to withdraw from the survey at any time without giving reasons and without any negative consequences. At last, all participants provided written informed consent for participation.

### Strengths and limitations of this study

This is the first survey in China to verify whether noise annoyance is an important factor affecting burnout.It is also the first study in China to examine whether emotional labor is a mediator between noise annoyance and burnout.A limitation of this study is that personality traits of participants are not measured using a thorough valid and reliable instrument since this is not the main objective of this study. In future exploration of the impact of personality traits on burnout in more detail, we will use more comprehensive and valid measurement scales.Another limitation is that the cross-sectional study design cannot determine causality of variables.In addition, our use of self-reported measures can also be considered a study limitation, which may introduce a risk of social desirability bias.
